## Abstract

Pleural effusions are common in adult intensive care unit (ICU) patients with respiratory failure. Ultrasonography‐guided therapeutic pleural drainage is widely used and associated with improved oxygenation and ventilatory parameters, but no randomised clinical trial data exist. This paper outlines the protocol and detailed statistical analysis plan for the Drainage Of Pleural Effusions in the ICU (DOPE‐ICU) feasibility trial. This is an investigator‐initiated, pragmatic, multicentre, open‐label, randomised, parallel‐group feasibility trial. Adults acutely admitted to the ICU with pleural effusion ≥ 2 cm and respiratory failure will be screened for inclusion. We will exclude patients with existing pleural or mediastinal drain, suspected or confirmed haemothorax, pneumothorax, empyema or pleural malignancy, coagulation deficiency or antithrombotic therapy incompatible with drainage, clinical indication for therapeutic pleural drainage and predefined severe hypoxaemic or hypercapnic respiratory failure, expected ICU stay < 24 h, pregnancy, imminent withdrawal of active therapy, or patients previously randomised in the trial. A total of 88 eligible patients will be allocated 1:1 to ultrasonography‐guided therapeutic pleural drainage with small‐bore catheter, with repeated drainage of repeated pleural effusions during ICU stay including readmissions within 90 days versus no therapeutic pleural drainage during ICU stay within 90 days unless pre‐specified escape criteria apply. The primary outcome is a feasibility outcome assessing group separation, i.e., proportion of patients receiving pleural drainage in ICU within 90 days. Secondary clinical outcomes include all‐cause 90‐day mortality, number of patients with one or more serious adverse events within 90 days, and absolute number of days alive without life support and out of hospital, respectively, in 90 days. Additional secondary feasibility and process outcomes will also be investigated. Data will be compared in the intension‐to‐treat population using generalised linear models adjusted for the stratification variable trial site. ClinicalTrials.gov identifier: NCT06709456. The DOPE‐ICU feasibility trial will assess whether randomised allocation to ultrasonography‐guided therapeutic pleural drainage or not in adult ICU patients with respiratory failure and pleural effusion is feasible. This will inform the design of a future large randomised clinical trial evaluating the clinical effects and safety of pleural drainage in this population.

## Introduction

1

Pleural effusions are common in adult intensive care unit (ICU) patients with reported prevalences between 31% and 81% when assessed ultrasonographically [1, 2, 3, 4, 5]. Common causes of pleural effusion in ICU patients are congestive heart failure, pneumonia, malignancies, hepatic hydrothorax, and nephrotic syndrome [6]. Pleural effusions have been associated with prolonged weaning from mechanical ventilation, increased mortality [7, 8], and longer ICU stay [8]. Pleural drainage is a frequent procedure in the ICU [5], particularly as a therapeutic intervention in ICU patients with respiratory failure [9]. It has been associated with improvements in the partial pressure of arterial oxygen to fraction of inspired oxygen (PaO_2_:FiO_2_) ratio and expiratory lung volumes, whilst carrying a low risk of peri‐procedural complications [10], especially when guided by ultrasonography [10, 11]. However, pleural drainage has also been negatively associated with survival, duration of mechanical ventilation, and ICU and in‐hospital lengths of stay [8]. No published randomised clinical trials have compared pleural drainage with no drainage in ICU patients with respiratory failure and pleural effusions [10]. A smaller Australian randomised trial allocating ICU patients to pleural drainage or no drainage, the Efficacy and Safety Outcomes of Drainage of Intensive Care Pleural Effusions (ESODICE) trial [12], was initiated in 2020 and had enrolled 37 of 52 planned patients by 2023; however, current progress is unclear. Another smaller randomised trial from Egypt allocated 60 mechanically ventilated ICU patients with uncomplicated pleural effusions to either single‐tap thoracentesis or pleural drain insertion and reported a reduction in the duration of mechanical ventilation with drain insertion [13]. In contrast, a recent non‐ICU randomised clinical trial evaluating therapeutic pleural drainage versus no drainage in 136 patients with cardiac failure and pleural effusions found no significant effects on any clinical outcomes [14]. Consequently, the effects of therapeutic ultrasonography‐guided pleural drainage are uncertain, as reflected in current international guidelines [15]. These provide recommendations for pleural drainage on a diagnostic basis, i.e., when malignancy or infection is suspected, but do not offer guidance on the indications for therapeutic pleural drainage [15]. Although expert consensus guidelines specifically addressing therapeutic pleural drainage in the ICU setting exist, they issue no specific recommendations on indications for conducting therapeutic pleural drainage, and their guidance is largely based on expert opinion or low‐certainty evidence, reflecting the limited availability of higher‐quality data [16]. Given the uncertainty regarding the balance of benefits and harms of therapeutic pleural drainage, together with its widespread use in ICUs, the evidence gap highlights the need for large, well‐designed randomised clinical trials. The aim of the Drainage Of Pleural Effusions in the Intensive Care Unit (DOPE‐ICU) feasibility trial is to assess feasibility and provide preliminary safety and outcome data to inform the design of such definitive large‐scale trials. Here we outline the trial rationale, methods, and detailed statistical analysis plan.

## Materials and Methods

2

### Trial Design

2.1

The DOPE‐ICU feasibility trial is an investigator‐initiated, pragmatic, multicentre, open‐label, randomised parallel group feasibility trial allocating acutely admitted adult ICU patients with respiratory failure and pleural effusion 1:1 to receive ultrasonography‐guided pleural drainage with a small‐bore catheter or not. Randomisation is centralised and web‐based according to concealed computer‐generated allocation sequence lists with permuted blocks of varying sizes, stratified for trial site.

This protocol and statistical analysis plan has been written according to the Standard Protocol Items: Recommendations for Interventional Trials (SPIRIT) 2013 statement [17], but confers to the updated SPIRIT 2025 statement (see Supporting Information S1 for the SPIRIT checklist) [18].

### Approvals, Registration and Ethics

2.2

The DOPE‐ICU feasibility trial (current protocol version 2.0 dated 30th July 2025) is approved by the Committee on Health Research Ethics in the North Denmark Region (N‐20240027) and prospectively registered at ClinicalTrials.gov (identifier: NCT06709456). It adheres to the Helsinki Declaration [19], the good clinical practise guidelines [20], and national Danish laws. Consent for enrolment follows Danish regulations on acute trials in temporarily incompetent patients, meaning that consent will be obtained as soon as possible after inclusion from the patient's next of kin and an independent physician, i.e., a trial guardian. Consent from the patient will be obtained if competence is regained.

In Denmark, the Danish Patient Compensation insures all trial participants.

### Setting

2.3

ICUs in university and non‐university hospitals in Denmark serve as trial sites. All sites are familiar with conducting large‐scale randomised clinical trials and are part of the Collaboration for Research in Intensive Care (CRIC) network. An updated list of participating sites can be found at ClinicalTrials.gov (identifier: NCT06709456).

### Inclusion Criteria

2.4

All adult patients (age ≥ 18 years), acutely admitted to the ICU, with drainable pleural effusion of ≥ 2 cm in either pleural cavity evaluated by ultrasonography, computed tomography or magnetic resonance imaging, and respiratory failure defined as receiving any oxygen supplementation in an open system, invasive or non‐invasive mechanical ventilation including non‐intermittent CPAP, or as hypercapnic failure with an arterial partial pressure of carbon dioxide (PaCO_2_) > 6.0 kPa and a pH < 7.35, will be screened for eligibility. To ensure timely identification of eligible patients, daily ultrasonographic examinations of pleurae in patients with respiratory failure will be encouraged.

### Exclusion Criteria

2.5

Patients will be excluded if they fulfil one or more of the following criteria: (1) Mediastinal drain or pleural drain in situ, (2) suspected or confirmed haemothorax, (3) suspected or confirmed pneumothorax, (4) suspected or confirmed pleural empyema, (5) suspected or confirmed pleural malignancy, (6) receives antithrombotic treatment or has a coagulation deficiency incompatible with conducting pleural drainage, and contraindications to reversal of this (clinical assessment), (7) clinically assessed indication for therapeutic drainage and (a) invasive or non‐invasive mechanical ventilation or non‐intermittent mask CPAP with PaO_2_:FiO_2_ ratio ≤ 13.3 kPa, (b) high‐flow humidified oxygen therapy with a flow ≥ 50 L/min and a PaO_2_:FiO_2_ ratio ≤ 13.3 kPa, or (c) persistent respiratory acidosis with a pH < 7.25 and PaCO_2_ > 6.0 kPa in spite of non‐invasive ventilation for > 1 h, (8) Withdrawal from active therapy or brain death is imminent, (9) expected ICU stay < 24 h, (10) pregnancy, (11) under coercive measures, i.e., ongoing involuntary hospital admission or under correctional authorities' jurisdiction, (12) consent not obtainable as per Danish legislation or (13) previously randomised in the DOPE‐ICU feasibility trial.

### Screening and Randomisation

2.6

All patients fulfilling the inclusion criteria will be screened by local investigators in the centralised web‐based screening system, through the electronic case report form (eCRF). Patients are eligible if they fulfil all inclusion criteria and none of the exclusion criteria.

Inclusion and exclusion of patients will be reported as according to the Consolidated Standards of Reporting Trials (CONSORT) 2025 statement [21].

### Interventions

2.7

Eligible patients will be randomised to either the intervention group or the control group.

#### Intervention Group

2.7.1

Patients in the intervention group will receive ultrasonography‐guided pleural drainage with insertion of a small‐bore catheter (typically pig‐tail type catheter, size 6–14 French) in the pleural cavity with pleural effusion of ≥ 2 cm as soon as possible, conducted by radiologists, intensivists, or surgeons, as per local standard. A time interval of up to 24 h from randomisation to intervention is expected to schedule pleural drainage and to allow for sufficient pausing of antithrombotic treatment or correction of coagulation deficiency if required. In case of bilateral pleural effusions ≥ 2 cm at randomisation, drainage of contralateral pleura will be conducted, expected within 24 h from insertion of the first pleural catheter. Inserted pleural catheters remain in situ and open until removed at clinicians' discretion according to local standards. If a new pleural effusion ≥ 2 cm is detected at any time during ICU stay within 90 days from randomisation, including during ICU readmissions, either contralaterally or ipsilaterally after pleural catheter removal, additional pleural drain insertion should be conducted.

#### Control Group

2.7.2

Patients allocated to the control group will not receive pleural drainage throughout the length of stay in the ICU including readmissions up until 90 days from randomisation, unless pleural drainage is judged clinically indicated, and one or more escape criteria (Table 1) are present as defined by (1) suspected or confirmed haemothorax, (2) suspected or confirmed pneumothorax, (3) suspected or confirmed pleural empyema, (4) suspected or confirmed pleural malignancy, (5) clinically assessed indication for therapeutic drainage and (a) invasive or non‐invasive mechanical ventilation or non‐intermittent mask CPAP with PaO_2_:FiO_2_ ratio ≤ 13.3 kPa, (b) high‐flow humidified oxygen therapy with a flow ≥ 50 L/min and a PaO_2_:FiO_2_ ratio ≤ 13.3 kPa, or (c) persistent respiratory acidosis with a pH < 7.25 and PaCO_2_ > 6.0 kPa in spite of non‐invasive ventilation for > 1 h. If a patient in the control group receives pleural drainage according to an escape criterion, the participant remains in the trial and additional pleural drain insertions within 90 days from randomisation follow the allocated strategy of no drainage. The participant will remain in the intention‐to‐treat population.

**TABLE 1 aas70233-tbl-0001:** Escape criteria for pleural drainage in the control group.

Escape criterion	Definition
Suspected or confirmed haemothorax	By radiographic or ultrasonographic assessment, or by clinical presentation. Assessed by clinicians.
Suspected or confirmed pneumothorax	By radiographic or ultrasonographic assessment, or by clinical presentation. Assessed by clinicians.
Suspected or confirmed pleural infection	By radiographic or ultrasonographic assessment, or by clinical presentation. Assessed by clinicians.
Suspected or confirmed pleural malignancy	Suspected or confirmed pleural lymphoma, pleural metastases or direct pleural invasion of cancer, or malignant mesothelioma. Detected by radiographic assessment, or by anamnesis and clinical presentation Assessed by clinicians.
Invasive or non‐invasive mechanical ventilation with PaO_2_:FiO_2_ ratio ≤ 13.3 kPa	Any mechanical ventilation including mask CPAP with a PaO_2_:FiO_2_ ratio ≤ 13.3 kPa in the most resent ABG conducted at the time of decision to conduct pleural drainage.
High‐flow humidified oxygen therapy with a flow ≥ 50 L/min and PaO_2_:FiO_2_ ratio ≤ 13.3 kPa	In the most resent ABG conducted at the time of decision to conduct pleural drainage.
Respiratory acidosis with a pH < 7.25 and PaCO_2_ > 6.0 kPa in spite of non‐invasive ventilation for > 1 h	In the most resent ABG conducted at the time of decision to conduct pleural drainage.

Abbreviations: ABG: arterial blood gas analysis; CPAP: continuous positive airway pressure; FiO_2_: fraction of inspired oxygen; ICU: intensive care unit; PaCO_2_: arterial partial pressure of carbon dioxide; PaO_2_: arterial partial pressure of oxygen.

#### Concomitant Interventions

2.7.3

All other interventions are at the discretion of the treating clinicians. In relation to respiratory failure, adherence to updated international clinical guidelines is recommended [22, 23, 24, 25, 26, 27, 28]. Co‐enrolment in other interventional trials will be permitted unless protocol requirements conflict, as determined and approved by the respective trial steering committees.

### Withdrawal and Discontinuation of Trial Intervention

2.8

If informed consent is not given or retracted at any time (according to Danish regulations), the patient will be withdrawn from the trial. Data registration for a withdrawn patient will continue if consent for this is given. Only the trial participant can demand deletion of already registered data. If so, all data will be deleted, and a new participant will be enrolled to obtain the full sample size.

Clinicians or investigators may deviate from the allocated pleural drainage strategy if the participant experiences intolerable adverse events suspected to be related to the allocated trial intervention or the clinicians in conjunction with the coordinating centre decide it to be in the best interest of the patient. In such cases the patient remains in the trial and the allocated strategy of pleural drainage will be reinstated as soon as it is considered acceptable within 90 days. If a patient after inclusion is subject to involuntary hospitalisation and treatment, the continued strategy of pleural drainage will follow local standards. The collection of data and follow‐up will continue, and the participant will remain in the intention‐to‐treat population.

Participants who are discharged to another ICU will be regarded as discharged from the ICU unless the receiving ICU is an active DOPE‐ICU feasibility trial site. If so, the patient will keep the allocated pleural drainage strategy during ICU admission up until 90 days after randomisation. All patients will be followed up for all outcomes.

### Outcome Measures

2.9

The primary outcome is a feasibility outcome evaluating group separation of the intervention, defined as the proportion of patients receiving pleural drainage during ICU stay within 90 days from randomisation.

Secondary outcomes are divided into three categories: secondary feasibility outcomes, secondary clinical outcomes, and secondary process outcomes:

#### Secondary Feasibility Outcomes

2.9.1

Proportion of included patients with one or more protocol violations, defined as: (1) patients allocated to pleural drainage who do not receive pleural drainage within 24 h from randomisation, (2) patients allocated to pleural drainage with bilateral pleural effusion ≥ 2 cm, who do not receive the second (contralateral) pleural drainage within 24 h from the primary drainage unless pleural drainage has receded < 2 cm, and (3) patients allocated to no pleural drainage who receive pleural drainage at any time during ICU stay within 90 days from randomisation, including ICU readmissions, except when escape criteria for pleural drainage are present as specified (see Table 1).Recruitment proportion, defined as the proportion of included patients out of the number of eligible patients, i.e., patients who comply with all inclusion and exclusion criteria over the duration of trial inclusion.Proportion of recruited patients with consent withdrawn for the use of data

#### Secondary Clinical Outcomes

2.9.2

All‐cause mortality within 90 days from randomisation.Proportions of patients with one or more serious adverse events within 90 days from randomisation defined as: (1) new pneumothorax requiring invasive treatment (drainage or surgery), (2) new haemothorax requiring red blood cell transfusion or other haemorrhagic complication related to pleural drainage requiring red blood cell transfusion, (3) new blood stream infection defined as any cultured microorganism from any blood sample except microorganisms clearly specified to be contaminants or likely contaminants by the microbiological department, and (4) new episode of invasive mechanical ventilation defined as endotracheal intubation or re‐intubation after extubation or tracheal decannulation.Absolute number of days alive without life support being the use of mechanical ventilation, renal replacement therapy, or circulatory support in the 90‐day period. Mechanical ventilation is defined as invasive or non‐invasive mechanical ventilation or CPAP. Intermittent CPAP is not considered mechanical ventilation. Renal replacement therapy is defined as any form of renal replacement therapy. In patients receiving intermittent renal replacement therapy, days between treatments are included as being with the use of renal replacement therapy. Circulatory support is defined as the use of continuously infused dopamine, norepinephrine, epinephrine, phenylephrine, vasopressin analogues, dobutamine, milrinone or levosimendan.Absolute number of days alive and out of hospital in the 90‐day period.

#### Secondary Process Outcomes

2.9.3

Proportion of patients with new pleural infection defined as any positive pleural fluid culture of any fungi or bacteria except pre‐defined contaminants being coagulase negative Staphylococci, Enterococci, and *Corynebacterium* species in any pleural fluid sampling conducted after 24 h from randomisation up until 90 days after randomisation.PaO_2_:FiO_2_ ratio in the arterial blood gas analysis (ABG) conducted in ICU closest to 24 and 72 h after randomisation. The FiO_2_ in open systems will be estimated from pre‐specified conversion tables (see Table 2)pH in the ABG conducted in ICU closest to 24 and 72 h after randomisation.PaCO_2_ in the ABG conducted in ICU closest to 24 and 72 h after randomisation.

**TABLE 2 aas70233-tbl-0002:** Conversion tables for calculating FiO_2_ in open systems.

Nasal cannula^a^											
Oxygen flow	0 L/min	1 L/min	2 L/min	3 L/min	4 L/min	5 L/min	6 L/min	8 L/min	10 L/min	12 L/min	14 L/min
FiO_2_	0.21	0.27	0.33	0.37	0.40	0.44	0.48	0.55	0.62	0.64	0.66

High‐flow humidified oxygen^b^																	
Total flow	Percentages represent oxygen concentration in the gas mixture, fractions the corresponding FiO_2_																
	21%	25%	30%	35%	40%	45%	50%	55%	60%	65%	70%	75%	80%	85%	90%	95%	100%
15 L/min	0.21	0.23	0.26	0.29	0.32	0.35	0.38	0.41	0.44	0.47	0.50	0.52	0.55	0.58	0.61	0.64	0.67
20 L/min	0.21	0.24	0.27	0.30	0.33	0.37	0.40	0.43	0.47	0.50	0.53	0.56	0.60	0.63	0.66	0.69	0.73
25 L/min	0.21	0.24	0.28	0.31	0.35	0.39	0.43	0.46	0.50	0.54	0.58	0.61	0.65	0.69	0.73	0.76	0.80
30 L/min	0.21	0.24	0.29	0.33	0.37	0.42	0.46	0.50	0.55	0.59	0.63	0.67	0.72	0.76	0.80	0.85	0.89
35 L/min	0.21	0.24	0.29	0.33	0.38	0.42	0.46	0.51	0.55	0.59	0.64	0.68	0.73	0.77	0.81	0.86	0.90
40 L/min	0.21	0.25	0.29	0.34	0.38	0.43	0.47	0.52	0.56	0.60	0.65	0.69	0.74	0.78	0.83	0.87	0.92
45 L/min	0.21	0.25	0.29	0.34	0.38	0.43	0.47	0.52	0.57	0.61	0.66	0.70	0.75	0.79	0.84	0.88	0.93
> 45 L/min	The FiO_2_ equals the oxygen concentration in the gas mixture																

Hudson mask or similar					
Oxygen flow	6 L/min	8 L/min	10 L/min	15 L/min	30 L/min
FiO_2_	0.45	0.50	0.54	0.59	0.65

Reservoir‐mask (non‐rebreather mask)	
Oxygen flow	≥ 10 L/min
FiO_2_	0.95

*Note:* Used for calculating the PaO_2_:FiO_2_ ratios for the secondary process outcome (i), PaO2:FiO_2_ ratios at 24 and 72 h after randomisation, and in baseline reporting. For flow‐rates or oxygen concentrations not included, the FiO_2_ will be extrapolated from the depicted. Adapted from Waldau et al. [29], Boumphrey et al. [30], Ritchie et al. [31], and Chanques et al. [32].

Abbreviation: FiO_2_: fraction of inspired oxygen.

^a^
Includes oxygen supplementation through T‐piece or speaking valve on tracheostomy.

^b^
Includes any high‐flow oxygen therapy through nasal cannula or high‐flow tracheostomy interface, at flow rates < 15 L/min, use conversion table for conventional nasal cannula above.

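### Table 2 footnote b converts blended high-flow oxygen below 15 L/min with a table that ignores the gas mixture, and read literally it can return an FiO2 above the concentration delivered

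*Protocol article*

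**What the plan says.** Section 2.9.3 (Secondary Process Outcomes) and Table 2 set out how FiO2 is estimated on open systems.

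- The nasal cannula part has one index, oxygen flow, and one FiO2 per flow, from 0.21 at 0 L/min to 0.66 at 14 L/min.
- The high-flow part has two indices: total flow down the side, and gas concentration across the top, where "Percentages represent oxygen concentration in the gas mixture". It starts at 15 L/min. For flows above 45 L/min the entry is that "The FiO_2_ equals the oxygen concentration in the gas mixture".
- Footnote b, which covers high-flow nasal cannula and high-flow tracheostomy interfaces, adds that below 15 L/min the user should "use conversion table for conventional nasal cannula above".

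The note under the table says that the conversion serves process outcome (i), PaO2:FiO2 at 24 and 72 h, and baseline reporting. Section 2.14.3 (Outcome Analyses) analyses that outcome as a mean difference from a Gaussian model and adds a supplemental baseline-to-72 h comparison. Tables 3, 4 and 5 record both flow and oxygen fraction on open systems.

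**The concern.** The cannula table describes added oxygen that the patient dilutes with room air. A high-flow setting below 15 L/min is a total flow of gas that may already be blended. Footnote b moves such a patient from a two-way table to a one-way table without saying which flow to enter, and without using the recorded fraction. If total flow is entered, the blend is treated as pure oxygen.

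A blend diluted with room air cannot give an FiO2 above its own concentration, so some of the resulting values are impossible. The error runs one way for blended gas: FiO2 too high, PaO2:FiO2 too low. At stake is the accuracy of one exploratory physiological outcome, its supplement and a baseline descriptor, for patients who have been turned down to a low high-flow setting.

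**Working it through.** **Inputs, all from Table 2.** Cannula FiO2 at 0, 1, 2, 3, 4, 5, 6, 8, 10, 12 and 14 L/min: 0.21, 0.27, 0.33, 0.37, 0.40, 0.44, 0.48, 0.55, 0.62, 0.64, 0.66. High-flow row at 15 L/min: 0.26 at 30%, 0.32 at 40%, 0.38 at 50%, 0.44 at 60%, 0.67 at 100%. Assumptions: PaO2 10 kPa for illustration, and linear interpolation between tabulated flows.

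**1. Literal reading against the delivered concentration.** There are 10 cannula flows from 1 to 14 L/min and 17 listed mixtures, so 170 combinations. Taking the flows in order, the cannula FiO2 exceeds the mixture concentration in 2 + 3 + 4 + 4 + 5 + 6 + 7 + 9 + 9 + 10 = 59 of them. For example, 5 L/min gives 0.44 for a 40% mixture, 10 L/min gives 0.62 for every mixture up to 60%, and 14 L/min gives 0.66 for every mixture up to 65%. No entry in the high-flow part exceeds its concentration.

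**2. What the 15 L/min row does with the mixture.** Every entry in that row follows, after rounding, from its 100% value: 0.21 + (0.67 - 0.21) x (c - 0.21)/0.79, with c the concentration. At 40%: 0.21 + 0.46 x 0.19/0.79 = 0.321, printed as 0.32. At 60%: 0.21 + 0.46 x 0.39/0.79 = 0.437, printed as 0.44. The cannula value at 14 L/min (0.66) continues only the near-pure end of the row (0.64 at 95%, 0.67 at 100%). The factor (c - 0.21)/0.79 is what footnote b loses.

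**3. Two ways of putting the mixture back, at 14 L/min.**
- *Added oxygen only:* enter F x (c - 0.21)/0.79 in the cannula table, with F the total flow. At 40%: 14 x 0.19/0.79 = 3.37 L/min, so FiO2 = 0.37 + 0.37 x 0.03 = 0.381.
- *Scaling:* 0.21 + (cannula FiO2 at F - 0.21) x (c - 0.21)/0.79. At 40%: 0.21 + 0.45 x 0.19/0.79 = 0.318.

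| Mixture | Footnote b, literal, 14 L/min | 15 L/min row | Added oxygen, 14 L/min | Scaling, 14 L/min |
|---|---|---|---|---|
| 30% | 0.66 | 0.26 | 0.306 (above 0.30) | 0.261 |
| 40% | 0.66 | 0.32 | 0.381 | 0.318 |
| 50% | 0.66 | 0.38 | 0.446 | 0.375 |
| 60% | 0.66 | 0.44 | 0.512 | 0.432 |
| 100% | 0.66 | 0.67 | 0.66 | 0.66 |

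Added-oxygen entry exceeds the concentration in only 2 of the 170 combinations, both at 14 L/min (0.253 for 25% and 0.306 for 30%). Scaling never exceeds it, because (cannula FiO2 - 0.21)/0.79 is at most 0.45/0.79 = 0.57. Entering total flow x c, another conceivable reading, still exceeds it in 32.

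**4. Effect on PaO2:FiO2 at PaO2 10 kPa, 14 L/min.**
- 40% mixture: literal 10/0.66 = 15.2 kPa; added oxygen 10/0.381 = 26.2 kPa; scaling 10/0.318 = 31.4 kPa; 15 L/min row 10/0.32 = 31.25 kPa.
- 30% mixture: literal 15.2 kPa; added oxygen capped at 0.30, 33.3 kPa; 15 L/min row 38.5 kPa.

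The proportional error (0.66/0.32 = 2.06 against the 15 L/min row at 40%) does not depend on PaO2.

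**5. Effect on a group mean.** With 88/2 = 44 patients per arm, all contributing a value, one patient misread by 11 to 16 kPa moves that arm's mean by 11/44 = 0.25 to 16/44 = 0.36 kPa.

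**The case against.** The best defence is that the cannula table is headed by oxygen flow. On that view the 15 L/min threshold only decides which table applies, and the user then enters what the table asks for. Room air at 10 L/min would carry no added oxygen and read 0.21, not 0.62. This reading removes all but two marginal cells. It has force: a careful analyst might well proceed that way. But the article does not write the step. Footnote b speaks only of flow rates, and the high-flow table it departs from uses total flow. A prespecified conversion should not depend on an unwritten step. The general note on extrapolating flows and concentrations that are not listed does not help either, because footnote b sets its own rule for this range.

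It can also be said that nothing decisive depends on this, and that stands. Section 2.14.1 declares all secondary outcomes exploratory, and section 2.14.3 reports them without p-values. The high-flow exclusion and escape criteria apply at 50 L/min or more, where Table 2 sets FiO2 equal to the concentration.

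Two stronger inferences are not supported. A reader might infer that patients being weaned would be classed as severely hypoxaemic. The example gives 15.2 kPa, above the 13.3 kPa threshold the protocol uses in its criteria; at FiO2 0.66, reaching that threshold needs a PaO2 of about 0.66 x 13.3 = 8.8 kPa or less. A reader might also infer a large error in the group comparison. The documents give no count of affected patients, and the same rule applies in both arms.

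**Conclusion.** The point holds as a minor defect in a stated rule. Taken literally, footnote b discards the gas mixture and gives impossible FiO2 values in 59 of 170 listed combinations, with a break from 0.32 to 0.66 between 15 and 14 L/min at 40%. For an affected patient in that example, PaO2:FiO2 is understated by roughly 11 to 16 kPa at an assumed PaO2 of 10 kPa; the range reflects which conversion is taken as the reference. If sites or analysts enter only the added oxygen, little error remains.

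The effect on the trial's results cannot be sized from the documents. It is confined to patients on blended high-flow below 15 L/min at the relevant blood gas, probably few, and to outcome (i), its baseline-to-72 h supplement and baseline reporting. The primary outcome, the sample size of 88 and the escape criteria do not depend on it.

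**What to change.** Before analysis, replace the last clause of footnote b with one explicit rule for high-flow below 15 L/min. Either of these works; choose one, since they differ (0.318 against 0.381 at 14 L/min and 40%):

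- FiO2 = 0.21 + (cannula-table FiO2 at that total flow - 0.21) x (concentration - 0.21)/0.79. This follows the scaling of the 15 L/min row, joins it closely and cannot exceed the mixture concentration.
- Enter the oxygen-equivalent flow, total flow x (concentration - 0.21)/0.79, in the cannula table, and cap FiO2 at the mixture concentration.

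Do not apply the 15 L/min row to all lower flows: it would assign 0.67 to 2 L/min of 100% oxygen, where the cannula table gives 0.33.

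The cost is one line of text and one line of code. Flow and fraction are already recorded, so no new data are needed. It is worth confirming that the case report form identifies high-flow interfaces, because the system types printed in Tables 3, 4 and 5 do not list them separately. The article states that the plan is to be published before any data analyses, so the rule can still be prespecified.
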